### Interventions

Participants will be randomly allocated into one of the two study arms: control (i.e., face-to-face consultation) and remote consultation (including teleconsultation, and video consultation). All patients, irrespective of the consultation type, will receive short text message reminders a few days before the visit.

Participants allocated into the control arm will be scheduled with face-to-face appointments as usual. All phone calls (except reminders for scheduled visits) performed by the physician during the study will be noted in the electronic case report form (eCRF). Per protocol, participants allocated in the control arm can receive up to 25% of physician-doctor interactions by phone (that is, one phone call allowed for three face-to-face appointments).

Participants allocated in the remote consultation arm will be scheduled remote visits, either phone or video consultation. In case of phone visits, the physician will call the main phone number provided by the patient and, in case of not receiving an answer, other phone numbers listed as contact numbers. In case of video consultation, the participant will receive an additional text message with the visit link. When clicking the link, a website with the video consultation system embedded will open in the default browser of the user. The video consultation platform of the physician pops up a message indicating that the patient is in the virtual waiting room. Patients will remain in the virtual waiting room until the physician starts the visit. A technical assistance is readily available for physicians who experience troubles with the system. In case the patient does not show up to the video consultation after a reasonable time, the physician calls the patient by phone. The date and hour of the phone call and the reason for the inability to connect are recorded in the eCRF.

Participants allocated in the remote consultation arm that require face-to-face visits will be excluded from the per-protocol analysis, and the reason for the face-to-face visit will be recorded in the eCRF. Participants allocated in the remote consultation arm and scheduled with a phone visit cannot be visited by video, whereas those scheduled for a video consultation can undergo up to 25% of phone visits. Phone contacts and their reason in patients in the video consultation arm will be recorded in the eCRF.

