### Participant timeline

Figure 1 summarizes the participant timeline. All participants, irrespective of the study arm, will be scheduled follow-up visits at a frequency determined by the physician based on the diagnostic and therapy of the baseline disease and will receive a reminder (either SMS or phone call) before each visit. Physicians can schedule and cancel appointments at their discretion. At least three visits should be scheduled in the study setting: the baseline visit (i.e., screening visit), intermediate visits (pre-defined by the physician based on the follow-up needed for managing the baseline condition), and the final visit (i.e., either the follow-up visit closest to 12 ± 2 months after enrollment or before in case of discharge or early discontinuation).

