**Fig. 1 Fig1:**
[figure not shown]
Participant timeline ^a^The frequency of the follow-up visits will be determined by the physician based on the diagnostic and therapy of the baseline disease and will receive a reminder (either SMS or phone call) before each visit. ^b^Either the follow-up visit closest to 12 ± 2 months after enrollment or before in case of discharge or early discontinuation

In addition to voluntary withdrawal, the following situations will lead participants in the remote consultation arms to discontinue the study: a change in their clinical status that requires face-to-face consultation and not following the procedures for remote consultation adequately. Patients allocated in the face-to-face arm will discontinue in case their health status discourages moving to the hospital for follow-up visits. The reasons for ending the study will be recorded in the eCRF.

The study will be temporarily interrupted if the local authorities or healthcare center managers decide to ban or limit face-to-face consultations because of the rapid spread of an infectious agent. This interruption can be partial in case banning face-to-face consultations does not affect all hospital services. The study will resume when face-to-face consultations are restored, and there is enough healthcare activity for adequate recruitment in all study arms. In case of a temporal interruption, the study will be automatically extended for a time that is at least equivalent to the interruption time.

The independent ethics committee can interrupt the study at any time in the advent of risk for participants, and the study sponsor can do it as well because of financial issues.

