### Data management and analysis

All data recorded in the eCRF will be stored in a REDCap platform hosted in a local server. The REDCap data will be transferred to a database, which will also contain the data extracted from the local EHR and the CHSS registries. All registries will be linked through the identification number of the Catalan Health Service.

Data recorded in the eCRF will be monitored for completeness and quality by a professional monitor working at the research office of the Hospital acting as sponsor. We will schedule periodic visits to assess the adherence of investigators to the study protocol and good clinical practices. The clinical monitor will release reports at the end of each visit.

A statistical analysis plan, with detailed analyses for each study outcome, will be performed after the last patient has attended the final visit and before the closure of the database.

The primary objective will be assessed using a non-inferiority analysis of the cumulative incidence of complications of the baseline disease between remote consultation (video and teleconsultation arms) and face-to-face consultation, using a non-inferiority margin of 2%. The analysis will be based on a modified binomial test to assess the non-inferiority of an experimental intervention vs. a control group in a three-arm trial [23]. The primary analysis will be conducted on a per-protocol study sample, which will include all participants who have finished the study and have not been withdrawn because of non-allowed visits using modalities other than scheduled. The intention-to-treat population, used for sensitivity analyses, will consist of all randomized patients completing at least one visit. Since the analysis will be based on an event rate, missing data will not be imputed.

The primary analysis will be replicated with patients stratified according to the following characteristics: hospital department, diagnostic, disease duration (chronic vs. acute or sub-acute), anatomic-therapeutic treatment groups, and GMA health risk group. The clinical and demographic characteristics of study participants will be described and compared between excluded/withdrawn participants.

The statisticians will be blinded for the allocation arm. The type I error will be set at 2.5% for the primary analysis and 5% for the rest of the analyses. All analyses will be conducted using R software (version 4.0 or higher) [24]. Data collected during the ECASeT trial will not be re-used.

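### A fallback phone call that the protocol itself directs can take a video patient with fewer than four contacts out of the primary per-protocol set, although phone is part of the pooled remote intervention

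*Protocol article*

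**What the plan says.** Four statements in the protocol article bear on this point.

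- **Fallback (Interventions).** "In case the patient does not show up to the video consultation after a reasonable time, the physician calls the patient by phone". The time of the call and the reason for the failed connection go into the eCRF.
- **Limit (Interventions).** For the remote arm, "those scheduled for a video consultation can undergo up to 25% of phone visits". Patients scheduled for phone may not be seen by video. The control arm has a limit of the same size, explained as "one phone call allowed for three face-to-face appointments".
- **Analysis set (Data management and analysis).** "The primary analysis will be conducted on a per-protocol study sample". It consists of participants who finished the study and "have not been withdrawn because of non-allowed visits using modalities other than scheduled". The intention-to-treat population is used for sensitivity analyses.
- **Schedule (Participant timeline).** "At least three visits should be scheduled in the study setting". The baseline (screening) visit is one of the three.

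The same section lists, as a ground for discontinuing remote-arm participants, "not following the procedures for remote consultation adequately". The primary comparison sets video and phone together against face-to-face.

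**The concern.** The fallback instruction and the 25% limit work against each other when a patient has few contacts. A physician who follows the instruction once can push the patient over the limit, and the per-protocol definition then gives a ground for leaving that patient out of the analysis on which the non-inferiority conclusion rests.

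The exclusion would not protect that conclusion. The question is whether remote follow-up is as safe as face-to-face follow-up, and a patient moved from video to phone has still had only remote contacts. The same phone contact is fully compliant in a patient for whom the physician chose phone, and potentially disqualifying in one scheduled for video.

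The patients at risk of exclusion are those who miss a video contact and have few visits planned. Both features may be related to the risk of complications, and the fallback trigger exists only in the remote arm. The loss could therefore be informative. Its direction cannot be told from the document.

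**Working it through.** **Inputs from the protocol article.** Limit of 25% and its illustration of one call to three appointments (Interventions); minimum of three visits including baseline (Participant timeline); second randomisation within the remote arm, video versus physician's choice, 3:7 (Screening, allocation, and blinding); 1068 per arm, and 252,000 visits from 121,400 patients (Sample size considerations).

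**Assumption.** The document does not give *p*, the chance that a scheduled video visit ends in a fallback call. I use 5, 10 and 20%, treat visits as independent, and count each fallback call as a phone visit.

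**1. Reproduce the limit.** One call with three appointments is 1/(1 + 3) = 25%, so the illustration matches the limit. In *k* contacts the number of calls allowed is floor(0.25*k*): none for *k* = 1 to 3, one for *k* = 4 to 7, two for *k* = 8 to 11.

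**2. Effect of one call.** It is 1/2 = 50% of two contacts, 1/3 = 33% of three and 1/4 = 25% of four. One call is over the limit below four contacts and within it at four or more.

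**3. Are fewer than four contacts realistic?** The minimum schedule leaves 3 − 1 = 2 visits after baseline. The centres' activity averages 252,000/121,400 = 2.08 visits per patient. That average covers all their outpatients, not trial participants, so it shows only that short schedules are plausible.

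**4. Chance of exceeding the limit.** For two contacts it is 1 − (1 − p)²; for three, 1 − (1 − p)³; for four, where two calls are needed, 1 − (1 − p)⁴ − 4p(1 − p)³.

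| Contacts | p = 5% | p = 10% | p = 20% |
|---|---|---|---|
| 2 | 10% | 19% | 36% |
| 3 | 14% | 27% | 49% |
| 4 | 1% | 5% | 18% |

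**5. Patients affected.** Randomised to video: 0.3 × 1068 ≈ 320; video chosen by the physician would add to this. If all had the same number of contacts:

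| Contacts | p = 5% | p = 10% | p = 20% |
|---|---|---|---|
| 2 | 31 | 61 | 115 |
| 3 | 46 | 87 | 156 |
| 4 | 4 | 17 | 58 |

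For two or three contacts the range is 31/1068 = 3% to 156/1068 = 15% of the remote arm.

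**6. When would more than half of video patients exceed the limit?** Setting the chance to 0.5 gives p = 1 − 0.5^(1/2) = 29% for two contacts and p = 1 − 0.5^(1/3) = 21% for three. For four contacts the numerical solution is 39%.

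**7. Alternative reading.** If fallback calls do not count towards the limit, this route excludes nobody.

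**The case against.** The strongest reply is that the exclusion is inferred. The only per-protocol exclusion that Interventions states outright is for remote-arm patients who need a face-to-face visit. Nothing says that a fallback call is a phone visit for the 25% count, or that passing 25% leads to withdrawal, and a call the protocol directs can be read as allowed. This stands as a limit on the claim: exclusion can follow, but it is not stated that it will. It does not remove the problem, because the two readings give different primary analysis sets.

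A second reply is that phone is a real departure for patients randomised to video. The second randomisation exists to secure a minimum number of video patients, the named test is for a three-arm trial, and the satisfaction survey counts three arms. A reader might infer that phone contact in a video patient departs from no allocation at all; that goes too far. Limiting the switch makes sense for describing video as such. It does not serve the primary contrast, which pools the two modalities.

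A reader might also infer that only the remote arm can lose patients to a phone limit. The control arm has its own 25% limit, with the same effect below four contacts. What is specific to the remote arm is the directed call. The control limit differs in purpose too, since it keeps the two compared arms apart.

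Finally, an article may leave counting rules to the full protocol or the analysis plan. That would answer a complaint about missing detail. Here, however, the article states an instruction, a limit and an analysis-set rule that conflict when followed as written.

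**Conclusion.** The point holds in a limited form. Any video-scheduled patient with fewer than four contacts who has one directed fallback call exceeds the 25% limit and can be left out of the primary analysis, although all contacts were remote. That part rests only on the document's own figures and on counting the call as a phone visit.

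The size depends on an unstated fallback rate. At 5 to 20% per visit and two or three contacts, about 31 to 156 of some 320 patients randomised to video are affected, or 3 to 15% of the remote arm. With four contacts the problem is much smaller.

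Two stronger readings are not supported. One is that most video patients would be lost. That needs a fallback rate above about 21% (three contacts) or 29% (two), no rate is given, and eligibility already requires digital literacy and the capacity to use the video software. The other is that the randomised comparison is broken. The loss may be informative, but neither its size nor its direction is known, and the intention-to-treat sensitivity analysis keeps these patients. The rule should still be corrected, because the per-protocol analysis is primary.

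**What to change.** Reconcile Interventions with Data management and analysis by adding one sentence to the per-protocol definition: for the pooled remote versus face-to-face comparison, substitution between phone and video within the remote arm, including a fallback call directed by the protocol, is not a deviation leading to exclusion.

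Keep the 25% phone/video limit only for any analysis by remote modality. The article specifies no video-versus-phone comparison. If one is added, it should say which contacts form the denominator and how the limit applies below four contacts. Leave the control-arm phone limit as it is.

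This changes an analysis-set rule, not patient care. It needs no new data, because phone contacts in video patients and their reasons are already recorded in the eCRF. It should be settled before outcome data by arm are seen.

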### Screening, allocation, and blinding

All consecutive patients who visited any of the participating departments between May 2022 and May 2024 will be informed about the study design and objective and will be offered to enroll in the trial. Patients who agree to participate will provide their informed consent, which will be signed in case of a face-to-face screening visit and oral in case of a remote visit. Patients who reject enrollment will be recorded in an anonymous registry. Once signed the informed consent, the investigator will assess the eligibility criteria and record them in the eCRF.

Patients will be randomly allocated in either of the study arms irrespective of the modality of the screening visit. Randomization will be balanced by medical specialty to prevent biases towards a particular diagnosis within study arms. To ensure a minimum number of participants who visited through video consultation, participants allocated to the remote consultation arm will be subsequently randomized to either video consultation or remote modality selection at physician discretion at a 3:7 ratio.

Centralized randomization will be automatically conducted by the randomization module of the REDCAP system used for the eCRF. The allocation will be informed to the administrative service, which will schedule all visits indicated by the physician during the investigated period following the criteria of each study arm. The health condition for which a patient has attended the screening visit will be considered the baseline disease for the study purposes.

Although study participants will be informed about the overall study objectives in the patient information sheet, they will not be aware of the study endpoints. In addition, the statisticians performing the analysis will be blinded to participant allocation. No rules for unblinding have been pre-defined in the study protocol.

### Data sources

To reduce the workload of participating investigators during visits, variables recorded in the eCRF will be limited to those that cannot be accurately retrieved from electronic health records (EHR), which will include both local hospital records and the dataset of the Catalan Health Surveillance System (CHSS), a central database of the Catalan Health System. By the time of submitting the study protocol to the ethics committee, all four study sites have separate and different EHRs. Throughout the following year, all the systems are to be unified into a single one and all the data from the different systems will be migrated. These EHR collect all the data related to the care received in the centers, clinical course, prescription, diagnostic images, laboratory tests, and administration, among others. The CHSS systematically collects and stores healthcare data on health status and resource utilization from all healthcare providers. The CHSS was originally designed for healthcare planning and has an automated validation system to identify internal inconsistencies between variables. Since the CHSS registries are used for control of capitation payments, they undergo external audits to ensure provider payment accuracy [16].

### Outcomes and variables

Table 1 summarizes the definitions and data sources of primary and secondary outcomes assessed in this trial. Complications and adverse reactions will be considered only if related to the baseline disease (i.e., the health condition for which the first study visit was scheduled). To prevent interference with routine practice, the investigator will have the option of recording the reference disease in a free-text field in the eCRF. The option of completing a field in English or Spanish linked to the ontologies of the ICD10 will also be available. If this field is not filled in, the ICD-10 code will be extracted from the free-text field. The investigator will also record the stage (if applicable) of the baseline disease and its severity.

**Table 1 Tab1:** Study outcomes and data sources

**Item**	**Domain definition**	**Measure and metrics**	**Data sources**^**a**^
**Primary outcome**			
Rate of complications^b^ of the baseline disease	A secondary disease, an accident, or a negative reaction (including adverse reactions to treatment) occurring during the course of the baseline disease and usually aggravating the illness.	Measure: events, as recorded in the eCRF. Metrics and aggregation: event rate (i.e., proportion of patients experiencing an event within each arm and the follow-up period).	Investigator-reported in the eCRF Local EHR.
**Secondary outcomes**			
Rate of severe complications of the baseline illness	A complication with significant impact on patient’s life and/or that require intervention by a healthcare professional	Measure: events, as recorded in the eCRF. Metrics and aggregation: event rate (i.e., proportion of patients experiencing an event within each arm and the follow-up period).	Investigator-reported in the eCRF Local EHR.
Rate of severe adverse reactions related to the treatment of the baseline condition	An undesired health event related to a drug administered to treat the baseline health condition	Measure: events, as recorded in the eCRF. Metrics and aggregation: event rate (i.e., proportion of patients experiencing an event within each arm and the follow-up period).	Investigator-reported in the eCRF
Rate of preventable hospitalizations	Hospitalizations due to illnesses secondary to the chronic diseases that can be managed in the outpatient setting^c^	Measure: events, as recorded in the eCRF. Metrics and aggregation: event rate (i.e., proportion of patients experiencing an event within each arm and the follow-up period).	Local EHR
Non-scheduled medical encounters related to poor control of the baseline disease	The following events will be considered: • Non-scheduled appointments (phone, videoconference, or face-to-face). • Visits to primary care services. • Visits to the emergency room. • Hospital admissions.	Measure: events, as recorded in the eCRF. Metrics and aggregation: event rate (i.e., proportion of patients experiencing an event within each arm and the follow-up period).	Investigator-reported in the eCRF Local EHR
Pharmaceutical prescriptions	The number of new prescriptions and renewals will be collected, along with the type of pharmaceutical prescription: long-term, acute process, or pro re nata.	Measure: ATC groups prescribed Metrics and aggregation: difference in number of ATC groups between baseline and last visit; the outcome will be measured as the mean and standard deviation, and median and interquartile range (i.e., 25^th^ and 75^th^ percentiles).	Administrative records.
Usability	Usability parameters will be collected using two approaches: • Computer System Usability Questionnaire. • Technical incidents reported by the investigators.	Measure: Questionnaire score and number of technical incidents. Metrics and aggregation: score, expressed as the mean and standard deviation, and median and interquartile range (i.e., 25^th^ and 75^th^ percentiles). Cumulative number of incidents.	Phone call administration by trained interviewers to 10% of the study sample. Investigator report to the eCRF.
Satisfaction	Satisfaction survey CSAPG included in the satisfaction survey plan of the Catalan Health System.	Measure: Questionnaire score. Metrics and aggregation: score, expressed as the mean and standard deviation, and median and interquartile range (i.e., 25th and 75th percentiles).	Phone call administration by trained interviewers to 10% of the study sample.
Care provision expenditure	Expenses related to each of the interventions.	Measure: cost in euros of the year. Metrics and aggregation: mean and standard deviation per patient.	Administrative records.

*EHR* electronic health record

^a^In outcomes gathered from more than one data source, discrepancies or inconsistencies between data sources will be addressed by the scientific committee before the closure of the database

^b^The severity of complications and adverse events will be recorded using a scale with four categories: (a) MILD: does not limit activity and does not require medical follow-up; (b) MODERATE: mild-to-moderate impact on activity or requires minimal medical intervention or monitoring; (c) SEVERE: significant impact on activity or requires medical care; (d) VERY SEVERE: life-threatening or results in major disability or significant incapacity for the subject

^c^The list of conditions considered has been retrieved from ambulatory care sensitive conditions and include ICD-10 categories related to ischemic heart (I20, I240, I248, I249), asthma (J45, J46), COPD (J20, J41, J42, J43, J44, J47), heart failure (I110, I50, J81), seizures (G40, G41, R56, O15), diabetes (E100-E108, E110-E118, E120-E128, E130-E138, E140-E148), hypertension (I10, I119), and iron-deficiency anemia (D501, D508, D509)

The follow-up period planned by the investigator for the baseline disease will be retrieved from the local EHR. Other variables collected from EHRs at baseline will include sex, age, area of residence, the number of active prescriptions at the end of the screening visit, and the comorbidity burden, summarized using the Adjusted Morbidity Groups (AMG). Briefly, the AMG is a case-mix tool that generates a summary index of health risk by considering all chronic conditions and recent acute diagnostic codes [17]. The tool allows stratifying patients into mutually exclusive health-risk groups and has shown a high predictive capacity of healthcare and resource use outcomes, including mortality, hospitalization, visits to primary care, polypharmacy, and overall expenditure [18, 19].

For homogeneity regarding the rate of preventable hospitalizations, we considered all hospitalizations due to any of the ICD-10 diagnostic codes listed as ambulatory care sensitive conditions [20] managed in the participating departments, including conditions related to ischemic heart disease (I20, I240, I248, I249), asthma (J45, J46), chronic obstructive pulmonary disease (COPD) (J20, J41, J42, J43, J44, J47), heart failure (I110, I50, J81), seizures (G40, G41, R56, O15), diabetes (E100-E108, E110-E118, E120-E128, E130-E138, E140-E148), high blood pressure (I10, I119), and iron-deficiency anemia (D501, D508, D509).

Usability will be assessed by passive and active surveillance. Study investigators will record non-attendances, as well as all technical incidences that occurred during the visit in an unstructured field of the eCRF. For active surveillance, a trained interview panel will contact by phone a subset of 100 participants randomly selected from all patients who have completed the final visit. Interviewers will administer the computer system usability questionnaire (CSUQ), a validated questionnaire aimed at measuring the users’ satisfaction with the usability of computer systems in scenario-based usability studies [21].

The users’ satisfaction with the quality of care received will be assessed using a validated tool encompassed within the satisfaction survey plan of the Catalan Health Service [22]. The questionnaire consists of 32 items that combine binary and multiple choice questions, 10-point assessment scales, and 2 open questions. An interview panel will administer the questionnaire by phone to a subset of 300 participants (100 per arm), randomly selected from all participants who have completed the final visit.

